Despite the growing body of evidence on the negative consequences of prenatal smoking for child development and despite extensive efforts to reduce the prevalence of prenatal smoking, a relatively large group of expecting mothers continues to smoke during pregnancy [1]. Factors associated with continued smoking during pregnancy are socioeconomic status (SES), nicotine dependence, and stress experienced during pregnancy [14, 15]. In general, women of low SES experience socioeconomic inequalities when it comes to financial resources, stability in living situation, general health, including more stress-related health problems and unhealthy lifestyle habits such as smoking [16, 17]. Stress plays an important role in initiating smoking and maintenance of smoking [18, 19]. According to the stress-coping model, smoking causes a temporarily reduction of negative affect and an increase in positive affect, which can be an explanation for the use of smoking as a coping strategy in situations of high stress [20]. Neurobiological models of addiction suggest that both stress and nicotine exposure trigger stress and reward circuits in the brain explaining why stress can increase the urge to smoke [18]. Moreover, high levels of stress hinder changing unhealthy lifestyle behaviors, such as smoking [21]. Increased activation of brain stress systems are thought to reduce an individual’s ability to cope with extra stressors and may strengthen the effects of acute nicotine exposure during abstinence, thereby contributing to the increased vulnerability to relapse caused by stress during periods of abstinence [19]. Elevated stress levels may thus explain why expecting women may fail to quit smoking, because pregnancy is a critical life event. Indeed, during pregnancy, many women experience some additional levels of psychosocial and pregnancy-related stress [22], due to physical changes related to pregnancy, concerns about childbirth and parenting, or relationship difficulties. These extra pregnancy related stressors can thus make smoking cessation even more challenging.

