### The current study

The current study will examine the effectiveness of a personalized 8-week lasting eHealth intervention “Together with Eva”, consisting of adapted parts of existing quit-smoking and stress-management interventions and an HRV-BF prototype application by means of a randomized controlled trial. “Together with Eva” includes psycho-education on stress, smoking (cessation), and pregnancy; a personalized stop-smoking plan; stress reducing exercises, comprising of HRV-biofeedback, and problem-solving techniques. Participants in the control group will receive access to a webpage developed for this study where they can read information comparable to the psycho-education of the intervention group. This information is however summarized and not interactive. Overall, the main research question of this study is the following:
Is the app intervention “Together with Eva” an effective intervention to support pregnant women to quit smoking during pregnancy and stay abstinent after giving birth? The primary outcome measure is self-reported smoking cessation. Secondary objectives of this study are to investigate whether;the intervention is effective on secondary outcomes (i.e. smoking behavior, perceived stress, birth outcomes, negative affectivity, parenting self-efficacy, pregnancy-related anxiety, feelings of mother-child bonding, and COVID-19 related stress),the intervention effect on smoking cessation is mediated by the reduction of perceived stress, and whether;variables such as program usage and experience, self-efficacy regarding smoking cessation, intrinsic motivation for life style behavior change, and pregnancy experience moderate the treatment effect.

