#### Mediator

##### Experienced stress

Experienced stress will be measured using the Dutch, short version of the Perceived Stress Scale (PSS; [62, 63]). This scale consists of 10 items about subjective experiences of unpredictability, lack of control, and burden during the last month, e.g. ‘In the last month, how often have you been angered because of things that were outside of your control?’ Participants indicate on a 4-point scale from ‘never’ to ‘always’ to what extend the items apply to them. Higher scores indicate higher perceived stress. Items and answer categories have been adapted to make it more suitable for our target group. Previous studies reported acceptable to good internal consistency of the PSS (Cronbach’s ﻿α 0.78–0.91; [64]).

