### Statistical analyses

The study will be performed according to the Consolidated Standards of Reporting Trials (CONSORT) Statement (see Fig. 3). All analysis will be done in SPSS version 26.0 and ﻿RStudio version 1.1.456 and a significance level of 0.05 will be used. Analyses will be performed conforming to intention-to-treat analysis, so that all randomized participants will be analyzed. We will explore baseline data to examine differences between the two different conditions and between the study completers and drop-outs. We will control for relevant covariates (i.e. SES, treatment history, maternal age, gestational age at birth, level of addiction, birth complications, way of delivery) by adding them to the models. Prior to the main analyses, outliers will be checked. Demographic outcomes will be compared using chi-square tests and independent sample t-tests.

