**Fig. 3 Fig3:**
[figure not shown]
Consolidated Standards of Reporting Trials (CONSORT) flow diagram

To examine the effectiveness of the eHealth intervention on the primary outcome, the number of women who quit smoking during pregnancy measured at post-intervention and follow-up, General Estimating Equations (GEE) using a logistic model will be performed. Potential covariates that will be included in the model are maternal age, depressive symptoms, gestational age, employment status, education level, level of addiction, and partner’s smoking status. To investigate the effectiveness of the intervention on secondary outcomes (i.e., smoking behavior, perceived stress, birth outcomes, negative affectivity, self-efficacy, mother-child bonding, intrinsic motivation, parenting self-efficacy, pregnancy-related anxiety) linear mixed models will be performed for each outcome variable separately. Furthermore, we will test whether the effect of the intervention (independent variable) on smoking cessation (dependent variable) is mediated by a change in perceived stress using a GEE model. Moreover, it will be tested whether program usage and experience, self-efficacy regarding smoking cessation, feelings of mother-child bonding, intrinsic motivation for life style behavior change, and pregnancy experience moderate the effect on smoking cessation (primary outcome), smoking behaviour, and perceived stress by adding the variables to the GEE model.

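### The mediation test uses a change in perceived stress, and baseline stress is in neither covariate list; if change is a simple difference, the stress-to-quitting path is understated unless change alone drives quitting

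*Protocol article*

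**What the plan says.** Among the secondary objectives, The current study asks whether "the intervention effect on smoking cessation is mediated by the reduction of perceived stress". The Statistical analyses section, in the paragraph after Fig. 3, makes this operational: the effect of the intervention on cessation "is mediated by a change in perceived stress using a GEE model". The sentence names no covariates and does not say how change is computed.

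The same section gives two covariate lists. The general one reads "i.e. SES, treatment history, maternal age, gestational age at birth, level of addiction, birth complications, way of delivery". The one attached to the primary GEE begins "Potential covariates that will be included in the model are maternal age, depressive symptoms, gestational age, employment status, education level, level of addiction" and ends with the partner's smoking status. Neither contains PSS at t0. The second does contain depressive symptoms, which may act as a partial proxy.

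The mediator is described under Experienced stress: "This scale consists of 10 items about subjective experiences of unpredictability, lack of control, and burden during the last month". No SD, t0-t1 correlation or expected effect on stress is given. On the link to smoking, the Introduction states that "high levels of stress hinder changing unhealthy lifestyle behaviors, such as smoking", and the Discussion also treats stress as an obstacle to quitting. Both statements are about how much stress a woman has, not only about how far it falls.

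**The concern.** A difference score carries its baseline with a minus sign. Women who start with high stress tend to fall further, partly through regression to the mean. If high stress also makes quitting harder, baseline stress is a common cause of a larger fall and of a lower chance of quitting. A large fall then marks two opposing things: success in reducing stress, and a bad starting point. The coefficient of change on quitting mixes them and moves toward zero. This holds whichever post-randomisation wave supplies the second PSS value.

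At stake is the trial's test of its own rationale, that a stress component helps women quit by lowering stress. A null result from the unadjusted model could be read as evidence that stress reduction does not matter when the model was poorly placed to see it. The arm-to-stress path is not biased, because arm is randomised, but it is estimated less precisely by an unadjusted difference than with baseline adjustment.

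**Working it through.** **No figure in the plan to reproduce.** The 160 women in Sample size calculation are for cessation at t1. The article gives no power or effect for mediation, so every numerical input below is an assumption.

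**1. Closed form.** Let M0 and M1 be PSS at t0 and after randomisation, with within-arm SDs s0 and s1 and correlation r. Let D = M1 - M0. Suppose the log-odds of quitting, given arm, are b·M1 + g·M0. On the linear approximation, the coefficient on D without M0 is

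[b·(s1² - r·s0·s1) + g·(r·s0·s1 - s0²)] / (s0² + s1² - 2·r·s0·s1).

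With s0 = s1 = 1 this is (1 - r)(b - g) / [2(1 - r)] = (b - g)/2, whatever r is.

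| What drives quitting | g | Coefficient on D | Understatement |
|---|---|---|---|
| Change alone | -b | b | none |
| Mostly t1 level | 0 | b/2 | 50% |
| t0 level adds half | b/2 | b/4 | 75% |
| t0 and t1 level equally | b | 0 | 100% |

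**2. Unequal SDs.** Take g = 0. With s1/s0 = 0.8 and r = 0.7: (0.64 - 0.56)/(1 + 0.64 - 1.12) = 0.08/0.52 = 0.15 of b. With s1/s0 = 1.25 and r = 0.7: (1.5625 - 0.875)/(1 + 1.5625 - 1.75) = 0.6875/0.8125 = 0.85 of b. Over SD ratios of 0.8 to 1.25 and r of 0.3 to 0.7, the g = 0 coefficient lies between 15% and 85% of b. The direction is stable; the size is not.

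**3. Depressive symptoms as a proxy.** Logistic simulation of 400,000 women with b = -0.50 per SD, r = 0.5 and an assumed correlation of 0.6 between depressive symptoms and t0 stress:

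| g | D only | D + depressive symptoms | With t0 PSS |
|---|---|---|---|
| 0 | -0.24 | -0.32 | -0.50 |
| -0.25 | -0.12 | -0.22 | -0.50 |
| -0.50 | 0.00 | -0.14 | -0.50 |

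With depressive symptoms the understatement runs from 1 - 0.32/0.50 = 36% to 1 - 0.14/0.50 = 72%. Repeat runs, and r = 0.7, move these by a few points.

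**4. Why t0 PSS cures it.** b·M1 + g·M0 = b·D + (b + g)·M0. Once M0 is in the model, the coefficient on M1 and the coefficient on D are both b, for any g. In simulation b is recovered at 98-101% of its size, including when g = -b.

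**5. Power for the indirect effect.** Simulated trials of 160 women, both paths required to be significant at 0.05. Assumed: arm effect on stress -0.5 SD, b = -0.6, g = 0, r from 0.5 to 0.7, quit probability at mean stress 20-40%.

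- D alone: 20-36%.
- D with depressive symptoms: 31-52%.
- PSS adjusted for t0 PSS: 58-84%.

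If change alone drives quitting (g = -b), the unadjusted difference does slightly better. At a 20% quit probability it gives 78% against 74% at r = 0.5, and 69% against 61% at r = 0.7.

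**The case against.** The strongest reply is that the article does not say what is being criticised. It speaks of a change without defining it. A residualised change, or PSS modelled across waves, would fit the words and could escape the bias. The mediation sentence names no covariates: one list is general, and the other belongs to the primary GEE and is called potential. A condensed article may leave model equations to the full protocol. This stands, so the point has to be conditional on the scoring. It does not remove the point, because a simple difference is the ordinary meaning of the phrase, and neither adjustment set that the article gives would protect it.

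A second reply is that the objective speaks of reducing stress. If change itself is the mechanism, then g = -b and there is no bias. That is correct, and adjusting for t0 PSS then costs a little power. But it is one special case, and the Introduction's own argument is about high levels of stress.

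A reader might infer that the path is understated by at least a third in every case. The documents do not support this. The range starts at none, and a lower end of about a third comes from assuming g = 0 with depressive symptoms in the model, while an upper end of all comes from leaving them out.

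A reader might also infer that true mediation will probably be missed because of this choice. That rests on an arm effect, a path coefficient and correlations that the article does not give. Even with t0 PSS, simulated power at g = 0 can be as low as 58%, so mediation could be missed anyway. The simulations also use one change and one outcome, not a repeated-wave GEE.

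**Conclusion.** The point holds in conditional form. If change is a simple difference and t0 PSS is left out, the stress-to-quitting coefficient is biased toward zero whenever stress level also affects quitting. With equal SDs the understatement is none at g = -b, about half at g = 0 and complete at g = b. With depressive symptoms in the model it is still roughly 36% to 72% for g = 0 to g = b, given the assumed correlation of 0.6. The power gap is illustrative, but at g = 0 the model with t0 PSS had clearly more power at every setting tried.

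This bears on the secondary mediation objective only. The primary comparison of cessation between arms is untouched. It is a cheap improvement to the analysis wording, not a flaw that threatens the trial.

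**What to change.** In the mediation sentence of Statistical analyses, define the mediator as post-randomisation PSS and put t0 PSS in both parts:

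1. A linear model of post-randomisation PSS on arm and t0 PSS.
2. A logistic model (or GEE) of quitting on arm, post-randomisation PSS and t0 PSS, with the chosen baseline covariates.

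Report the indirect effect with a bootstrap interval. If the team prefers to keep a change score, it should state how it is scored and add t0 PSS; the stress coefficient is then identical.

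Cost: one extra parameter per model and no new data, since any change from t0 already needs t0 PSS. If change alone is the mechanism, the estimate stays unbiased, and the loss of power was 4 to 8 percentage points in the runs above.

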### Patient and public involvement

The design of the content of both the eHealth intervention and the control condition was achieved by co-creating processes with focus groups of women with low socioeconomic backgrounds, who either successfully quit smoking or struggled with quitting smoking during pregnancy. Data collection is carried out in collaboration with midwives and nurses from various midwifery practices and hospitals throughout the Netherlands.

## Discussion

The objective of this study is to examine the effectiveness of an eHealth intervention to help pregnant smoking women quit smoking. In contrast to other smoking-cessation interventions, this app-intervention particularly focuses on teaching women new stress-coping techniques. Such a component has been missing in existing stop-smoking programs. Stress is a common factor among smokers that hampers quitting and may result in relapse, in particular for women of low socioeconomic backgrounds**.** Smoking is a common behavior to alleviate feelings of tension. Despite this co-occurrence of smoking with high levels of stress among low SES pregnant women, we still lack an intervention that also supports pregnant women in learning new stress-coping skills. Learning new stress-coping skills might not only help these women quit smoking during their pregnancy, but can also help women stay abstinent after the birth of their baby.

‘Together with Eva’ is developed for women with low SES by means of easy and understandable language, attractive design, many repetitions of both text and exercises, positive feedback, and instruction videos of the different components of the application (i.e. stop-smoking plan, diary, breathing exercises). This was done in co-creation with women from the target group. Thereby, we expect to achieve the most beneficial results for this group of smoking pregnant women. As, once developed, the intervention can be made available to users for a low price, is easily accessible, and easy to implement into the health care system, we expect that this app-intervention will be a useful tool both for health care professionals to offer to their patients and for the pregnant women to receive support with quitting smoking during pregnancy. All in all, a personalized intervention for this target group is needed to further reduce inequalities in perinatal and maternal outcomes in in high income countries.

### Status of the trial

After receiving permission by the Medical Ethics Committee to start with the inclusion of participants, the first participants were included in July 2020. Currently, data collection is ongoing. The main results are expected to be published in 2022.

## Data Availability

The datasets generated and/or analyzed during the current study will be available from the corresponding author on reasonable request.

## Abbreviations

ACT: Acceptance and Commitment Therapy
BZS: Beleving van de Zwangerschap Schaal
CBT: Cognitive Behavior Therapy
CONSORT: Consolidated Standards of Reporting Trials
DASS: Depression, Anxiety, Stress Scale
HRV: Heart Rate Variability
HRV-BF: Heart Rate Variability Bio-feedback
HSI: Heaviness of Smoking Index
IBQ: Infant Behavior Questionnaire
METc: Medical Ethics Committee
NTR: Netherlands Trial Register
PES: Pregnancy Experience Scale
PRAQ: Pregnancy-related Anxiety Questionnaire
PSS: Perceived Stress Scale
RCT: Randomized Controlled Trial
SDK: Software Developer Kit
SENR: Self-efficacy in the Nurturing Role questionnaire
SES: Socio-economic status
SSFSL: Stress- and Smoke Free Start of Life
TSRQ: Treatment Self-regulation Questionnaire
t0: baseline assessment
t1: second assessment
t2: third assessment (first follow-up)
t3: fourth assessment (second follow-up)
UEQ: User Experience Questionnaire
VUmc: VU University Medical Center
